##### Inclusion Criteria

The inclusion criteria are children aged 7–13 years (inclusive) with overweight or obesity, as defined by the Centers for Disease Control and Prevention (i.e., BMI ≥ 85th percentile), and living in Victoria, Australia [42]. Children will be generally healthy, defined as an absence of clinical or comorbid conditions that require medical clearance to participate. Children with a learning or behavioral disability will be included if their condition does not impact their ability to engage in the program. Children will also have at least one parent/caregiver who will accompany and support them with study/program activities and can provide informed consent. Children will meet all inclusion criteria of the web-based program as it would typically run, including being able to attend weekly coaching appointments scheduled on weekdays at 15:00–21:00. There are no other inclusion criteria for parents/caregivers.

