### 2.6. Outcome Measures

Outcome measures will be self-reported via surveys administered online, at baseline, post-program completion (10 weeks), and 6- and 12-months post-program completion. Participants allocated to the control group will be asked to complete an additional set of surveys following the 10 week control period. All study assessments will be administered online via a Research Electronic Data Capture (REDCap) [46,47] link, Australian Eating Survey (AES) [48], or Youth Activity Profile (YAP) [49] link, and distributed to participants via email.

Qualitative data will also be collected online through video conferencing and real-time transcribing platforms (Zoom [50], Otter.ai [51]) at 3 months post-program completion.

All study assessments, including study surveys and interviews, will be completed by both the participating child and parent/caregiver. All outcome measures will be self-reported by participants to complement the virtual nature of the intervention and include the participation of families from all geographic locations of Victoria. A study by Chai and colleagues supports the use of parent-reported measurements that are collected online for web-based lifestyle programs [52]. The study found that Australian parents of primary-school-aged children were relatively accurate in reporting their child’s anthropometric measurements, including their weight and height [52]. 

The primary outcome measure is the change in the child’s BMI z-score. Secondary outcomes include (the change in) the child’s BMI z-score, waist circumference, dietary intake, physical activity, quality of life, and the participating child and parent/caregiver’s experience of completing the program. Details on the collection of the outcome measures are summarized in Table 1.

The web-based program also includes surveys to be completed by participants as a part of the program activities. Data collected from these surveys may supplement data collected by study investigators, to inform outcome measures. 

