### 2.7. Data Analysis

All statistical analysis of quantitative data will be performed using IBM SPSS Statistics version 25 [46] and methods were confirmed with and reviewed by the Monash study statistician ([name]). 

The primary focus of this study is to test whether the web-based program has an effect on BMI z-score over a 10-week period. An independent *t*-test will be used to compare the difference in the mean change in BMI z-score between Cohort 1 and 2 from baseline to 10 weeks. Independent *t*-tests will also be used to compare the differences in the quantitative outcome measures between cohorts from baseline to 10 weeks. A 2 × 2 mixed ANOVA will be conducted to investigate the impact of the web-based program (between factor: web-based program vs. control) on BMI z-score from baseline to 10 weeks (within factor). Separately, mixed model ANOVAs will also investigate the impact of the web-based program on the secondary outcome measures (i.e., WC, diet quality score, physical activity score, and quality of life scores) from baseline to 10 weeks. The impact of being waitlisted (Cohort 2) will be explored to ascertain whether receiving the web-based program following 10 weeks of waiting will differ on the quantitative outcome measures from Cohort 1 over time. If being waitlisted does not have an impact on the quantitative outcome measures (as anticipated), a one-way repeated measures ANOVA will be used to assess the effect size of the web-based program on quantitative outcome measures overtime with greater certainty (i.e., power). Independent *t*-tests may also be used to compare the differences in the mean changes in quantitative outcome measures between cohorts or compare the mean differences in quantitative outcome measures for all participants at immediately pre-program (baseline or post-10-weeks waitlisted period) and post-program completion. 

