## Figures and Tables

**Figure 1 nutrients-15-02909-f001:**
[figure not shown]
Randomized controlled trial with a waitlisted control group study design. Dashed box = optional post-program research follow-up activity.

**Table 1 nutrients-15-02909-t001:** Outcome measures and measurement methods.

Outcome Measure	Collection Method/Tool	Details
BMI z-score/change in BMI z-score	Calculated from height and weight	Participants will be asked to report the participating child’s standing height and weight, measured at home or by a health professional. Participants will be provided with a measurement kit, including a height ruler and measuring triangle and instructions on how to measure height and weight accurately (posted to participants from BHC following their initial calls) [52].
Waist circumference	Tape measure	Participants will be asked to report the participating child’s waist circumference, measured at home or by a health professional. Participants will be provided with a measurement kit, including a tape measure, and instructions on how to measure waist circumference accurately (posted to participants from BHC following their initial calls).
Dietary intake (diet quality score)	AES [48]	Participants will be asked to complete the AES, based on the participating child’s dietary intake. The AES is a validated food frequency questionnaire used to assess usual dietary intake of individuals aged 2 years and above [48].
Physical activity (physical activity score)	YAP [49]	Participants will be asked to complete the YAP, based on the participating child’s engagement in physical activity. The YAP is an online tool used to assess an individual’s physical activity, namely collecting information on the individual’s physical activity behavior/patterns to generate a physical activity score. The tool was developed in the United States and, for the purpose of this study, has been customized to reflect common word choices and expressions used in Australia [49].
Quality of life (quality of life score)	PedsQL [53]	Participants will be asked to complete the PedsQL (both the parent and child versions), based on the participating child’s quality of life. The PedsQL is a brief and validated questionnaire that assesses health-related quality of life in children and adolescents [53].

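### The within-group and follow-up analyses use raw waist circumference in growing children with no untreated comparator, so ordinary growth is mixed with program effect and counts against the program

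*Protocol article*

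**What the plan says.** Eligibility covers a growth period: "The inclusion criteria are children aged 7–13 years (inclusive) with overweight or obesity". Table 1 describes waist as a tape reading: "Participants will be asked to report the participating child’s waist circumference, measured at home or by a health professional". No z-score, percentile or ratio is named for it, although the table gives BMI as a z-score and diet, activity and quality of life as scores. Height is collected as well: "Participants will be asked to report the participating child’s standing height and weight, measured at home or by a health professional".

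Surveys are scheduled "at baseline, post-program completion (10 weeks), and 6- and 12-months post-program completion", and "Participants allocated to the control group will be asked to complete an additional set of surveys following the 10 week control period". The last paragraph of the Introduction includes waist at 6 and 12 months in the primary aim. Under Section 2.2, the control group receives the program in the term or midterm after its wait.

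Section 2.7 contains two kinds of waist analysis:

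- **Randomised.** "mixed model ANOVAs will also investigate the impact of the web-based program on the secondary outcome measures (i.e., WC, diet quality score" and the other listed scores, with the sentence ending by limiting the window to baseline to 10 weeks. Independent t-tests between cohorts cover the same window.
- **Within-group.** If being waitlisted has no impact, which the authors expect, "a one-way repeated measures ANOVA will be used to assess the effect size of the web-based program on quantitative outcome measures overtime". The section also permits a comparison of all participants immediately pre-program with post-program completion, where the pre-program value for the control group is its post-wait assessment.

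**The concern.** A child whose body proportions stay the same still gains waist centimetres while growing. In a randomised comparison this does not matter. In a within-group analysis it does, because the change over time is the estimate, and Section 2.7 calls that estimate the effect size of the program. BMI is protected to a large extent by its age and sex standardisation; waist, the other adiposity outcome, is not.

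At stake is how the longer-term waist result is read. A modest rise at 6 or 12 months could be ordinary growth, and a flat waist could be an improvement. The Introduction presents evidence beyond the short term as a gap in the literature, so these results are likely to be read closely.

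**Working it through.** **Plan's own figure.** There is none to reproduce: the protocol article gives no expected waist effect, no SD of waist change and no growth rate. Its one sample-size calculation concerns BMI z-score.

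**Inputs from the document.** Program of 10 weeks; follow-up 6 and 12 months after it; 59 per group; 30% attrition; four school terms a year.

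**Inputs assumed.** Waist growth 1–3 cm/year; height growth 5–6 cm/year; SD of waist change 5 cm; an example child of 145 cm with an 82 cm waist.

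**Step 1: growth in raw waist with no program effect.** Growth = rate × weeks / 52.

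| Interval from baseline | Weeks | 1 cm/y | 2 cm/y | 3 cm/y |
|---|---|---|---|---|
| End of program | 10 | 0.19 | 0.38 | 0.58 |
| 6 months post-program | 10 + 26 = 36 | 0.69 | 1.38 | 2.08 |
| 12 months post-program | 10 + 52 = 62 | 1.19 | 2.38 | 3.58 |

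**Step 2: does it bias the comparison?** Completers per arm: 59 × 0.7 = 41.3, taken as 41, or 82 pooled. Trials were simulated with no program effect.

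- Between arms at 10 weeks: mean difference about 0, and 4.8–5.2% of trials significant at the 5% level. Growth cancels.
- Pooled change from baseline to 12 months post-program: standard error 5 / √82 = 0.55 cm. A significant worsening was declared in about 58%, 99% and 100% of trials at 1, 2 and 3 cm/year.

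**Step 3: does waist-to-height ratio solve it?** The example child starts at 82 / 145 = 0.5655. Change after 62 weeks with no program effect:

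| Waist growth | Height +5 cm/y | Height +6 cm/y |
|---|---|---|
| 1 cm/y | −0.014 | −0.019 |
| 2 cm/y | −0.007 | −0.011 |
| 3 cm/y | +0.001 | −0.003 |
| 4 cm/y | +0.009 | +0.005 |

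The ratio is flat only when waist grows at height growth × 0.5655, which is 2.83 cm/year (5 × 0.5655) to 3.39 cm/year (6 × 0.5655). With slower waist growth it falls, which looks like benefit.

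**Step 4: timing of the two cohorts.** Four terms a year put program starts about 52 / 4 = 13 weeks apart. Measured from enrolment, Cohort 2 reaches 12 months post-program at about 62 + 13 = 75 weeks, and so carries 13/52 × (1 to 3) = 0.25–0.75 cm more growth than Cohort 1. Measured from its post-wait assessment at 10 weeks, its interval is 75 − 10 = 65 weeks, and the excess is 3/52 × (1 to 3) = 0.06–0.17 cm.

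**The case against.** The case against has several parts.

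- **The sentence that names waist is unaffected.** A reader might infer from it that all waist results are biased. The document does not support this: the sentence is limited to baseline to 10 weeks between randomised arms, and step 2 shows no bias there. This stands.
- **The repeated-measures analysis is conditional, does not name waist and does not list its time points.** True. But it covers the quantitative outcome measures, waist is one of them, its condition is expected to be met, and the stated aim extends to 6 and 12 months.
- **The scale of a secondary outcome can be left to an analysis plan.** In general, yes. Here Table 1 names the analysed form of the other quantitative outcomes and leaves waist as a tape reading. If an analysis plan already standardises waist, only the interpretive statement is needed.
- **Waist-to-height ratio does not cure the problem.** A reader might infer that switching to the ratio avoids growth altogether. Step 3 shows otherwise; assuming a constant ratio in order to show that the ratio is constant would be circular. What is missing is an untreated comparator, and no rescaling supplies one. This stands and shapes the fix.
- **A growth artefact between Cohorts 1 and 2 is not established.** It would be material only if Cohort 2 were measured from enrolment. The text does not fix that origin for the over-time comparison, and its all-participant pre/post comparison uses the post-wait value. This stands.
- **Reversal of a real benefit is not shown.** A reader might infer that the 12-month result will reverse a true effect. The document gives no expected waist effect, so only the direction of the bias can be stated.

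**Conclusion.** The point holds for the uncontrolled analyses of one secondary outcome. The one-way repeated measures ANOVA and the all-participant pre/post comparison, applied to raw waist in children aged 7–13, count ordinary growth as part of the program's effect. The direction is against the program as long as waist increases with age. The size is about 0.7–2.1 cm at 6 months and 1.2–3.6 cm at 12 months post-program, and 0.2–0.6 cm for a pre/post comparison over the 10 program weeks. All these figures rest on assumed waist growth of 1–3 cm/year; the significance rates also rest on an assumed SD of 5 cm and 82 completers. The randomised 10-week waist comparison and the primary BMI z-score outcome are not affected.

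**What to change.** In Section 2.7 and Table 1:

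1. Keep raw waist in centimetres for the randomised comparison at 10 weeks.
2. For the within-group and follow-up analyses, use an age- and sex-standardised waist score, or waist-to-height ratio from the height already reported, and give raw waist descriptively.
3. When the cohorts are compared over time, measure both from program start, using the post-wait assessment for Cohort 2.
4. State that waist change after 10 weeks, on any scale, is uncontrolled and is not by itself evidence of a program effect.

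The cost is a few sentences and one derived variable, with no new data, visits or participants. A standardised score also needs a named reference population, which the document does not give for waist. There are two downsides. Error in reported height enters the ratio. The ratio also reduces growth drift without removing it, and can fall with no program effect if waist grows proportionately more slowly than height. Item 4 does not depend on any growth assumption and should be kept whichever scale is chosen.

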### 2.2. Study Design

This study is an RCT with a qualitative component and a waitlisted control group (Figure 1). This study is pragmatic in nature because it has been developed to evaluate the web-based program as it would typically be delivered. 

The 10-week web-based program will be administered by the administrating organization, Better Health Company (BHC), and is delivered during the year at primary school terms and midterms. In Australia, there are four school terms per year. The midterm programs will start approximately 6 weeks into the school term. Participants will be recruited for a school term or midterm program; a new recruitment cycle will begin, at the latest, 2 weeks prior to the commencement of the next earliest term or midterm program. Participants recruited during a school term or midterm recruitment cycle will only be considered for a school term or midterm program, respectively. Following study enrolment, participants allocated to the intervention group (Cohort 1) will complete the program in the subsequent commencing school term or midterm, whereas participants allocated to the control group (Cohort 2) will complete the waitlist control period in the next commencing school term or midterm. Participants allocated to the control group will not receive any intervention during the 10 weeks control period and will receive the (same) web-based program in the school term or midterm following the waitlist control term. Study involvement for each participant will run from baseline to 12-months post-program completion. 

Families who consent to the study will be randomized into the intervention or waitlisted control group. The randomization schedule was generated using block randomization (1:1 ratio) from Research Randomizer [41]. Group allocation will not be communicated to the BHC. Instead, study investigators will allocate participants to the respective school term or midterm in BHC’s data management system. In doing so, BHC’s health coaches, who are assigned to and have direct contact with families during the program, will be blinded to the study allocation.

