#### 2.3.2. Sample Size Estimation

The primary outcome will be the change in BMI z-score from baseline to 10 weeks. An a priori power analysis was conducted using G*Power version 3.1.9.4 [43] to estimate the sample size needed to detect a difference in the mean change in BMI z-score between the intervention and control group from baseline to 10 weeks using a *t*-test. The sample size estimation accounted for a possible reduction in BMI z-score within the control group, an effect size based on BHC’s pilot data, and a 30% attrition rate based on previous trials on a similar program (trials on the MEND program reported a 30% attrition) [44]. The effect size based on the change in BMI z-score and informed by pilot data was 0.6 (i.e., medium effect size using Cohen’s (1988) [45] criteria). With a 5% significance and 80% power, this study aims to recruit *n* = 118 participants (*n* = 59 intervention group; *n* = 59 control group) to observe a difference in the primary outcome measure between groups with this effect size using a *t*-test. 

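### The waitlist check that decides pooling compares Cohort 2 only after a wait Cohort 1 never faces, so loss during the wait can hide, create or distort a waitlist effect

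*Protocol article*

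**What the plan says.** Section 2.2 (Study Design) randomises families 1:1. Cohort 1 starts the program at the next available school term or midterm slot. Cohort 2 first goes through a 10-week control period and then "will receive the (same) web-based program in the school term or midterm following the waitlist control term".

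Section 2.7 (Data Analysis) defines the waitlist question as "whether receiving the web-based program following 10 weeks of waiting will differ on the quantitative outcome measures from Cohort 1 over time". The consequence follows in the next sentence: "If being waitlisted does not have an impact on the quantitative outcome measures (as anticipated"), a one-way repeated measures ANOVA estimates the program's effect size over time, with the stated aim of gaining power. The same section says that independent t-tests may compare mean changes between cohorts, or compare readings for all participants immediately before and after the program. For Cohort 2 the pre-program reading is the one taken at the end of the waiting period.

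The quantitative outcome measures are BMI z-score, waist circumference, diet quality, physical activity and quality of life (Section 2.7 and Table 1). Starting or finishing the program is not among them.

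On loss to follow-up, Section 2.3.2 gives a single figure, "a 30% attrition rate based on previous trials on a similar program", not split by cohort or by period.

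**The concern.** Cohort 1 contributes its program response from the first slot after enrolment. Cohort 2 contributes only if a family is still there after the wait, and any gap before its slot, and then provides post-program data. That is a selection step after randomisation with no counterpart in Cohort 1. If the families who leave while waiting would have responded differently from those who stay, the contrast mixes the effect of waiting with the effect of who remained.

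Two things depend on it. The check decides whether the cohorts are pooled, and the same selected Cohort 2 then feeds the pooled estimate. Also, a family that gives up during the wait leaves no trace in the outcome measures used to judge waiting, although the Introduction lists long waiting lists among the failings of existing services. The waits it cites for specialist clinics are 12 months or longer, so the parallel with a 10-week trial wait is loose.

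**Working it through.** **1. The plan's own figure.** Inputs from Section 2.3.2: effect size "informed by pilot data was 0.6", 5% significance (two-sided assumed), 80% power, 30% attrition. A two-sample t-test needs 44.6, so 45 per arm. Then 45 × 1.3 = 58.5, so 59 per arm and 118 in total, which matches "this study aims to recruit *n* = 118 participants". This figure is for the primary program-versus-control contrast. The article gives none for the waitlist contrast.

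**2. Who can enter the waitlist contrast.**

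| | Cohort 1 | Cohort 2 |
|---|---|---|
| Pre-program reading | baseline | end of the 10-week wait |
| Must remain through a wait first | no | yes |
| Post-program reading needed | yes | yes |

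A Cohort 2 family lost during the wait has a baseline reading only. It has no change score over the program and is left out of a classical repeated measures ANOVA. The exclusion follows from the contrast and the tests, without any written rule.

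**3. Numbers left (illustration).** With 30% loss, 59 × 0.7 = 41.3, about 41 per arm. If Cohort 2 lost a further 30% while waiting (assumed), 59 × 0.7 × 0.7 = 28.9, about 29. The difference detectable with 80% power moves from 0.63 SD (41 v 41) to 0.69 SD (41 v 29). This is lost precision, separate from the selection issue.

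**4. Size of the selection shift.** Assume a fraction p of Cohort 2 leaves during the wait, those lowest on a standard normal score for the tendency to stay, and that this score correlates r with program response. Loss common to both cohorts is ignored. The mean response of those who stay moves by

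shift = r × φ(z_p) / (1 − p), in SD units,

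where z_p is the p-quantile of the standard normal and φ its density.

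| Loss p | φ(z_p)/(1 − p) | r = 0.2 | r = 0.3 | r = 0.5 |
|---|---|---|---|---|
| 10% | 0.195 | 0.04 | 0.06 | 0.10 |
| 20% | 0.350 | 0.07 | 0.10 | 0.17 |
| 30% | 0.497 | 0.10 | 0.15 | 0.25 |

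Simulation gives the same values to within 0.01. With r = 0 there is no shift. With negative r the sign reverses.

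**5. Direction.** Apparent Cohort 2 minus Cohort 1 difference in SD at 30% loss (positive = better response in Cohort 2):

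| True waiting effect | r = +0.5 | r = −0.5 |
|---|---|---|
| −0.3 | −0.05 | −0.55 |
| 0 | +0.25 | −0.25 |
| +0.3 | +0.55 | +0.05 |

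The same loss hides a real effect in two cells, creates a false one in two and enlarges a real one in two. When the true effect is zero and the shift is 0.25 SD, a 5% test with 41 v 29 families reports a difference about 17% of the time.

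**The case against.** The strongest reply is that the article names no analysis set for this contrast. It does not say that families lost while waiting are excluded, and its wording about receiving the program after a wait can be read simply as a description of Cohort 2's allocation. Analysis sets and missing-data rules are usually left to a fuller document. This stands to the extent that no explicit exclusion can be attributed to the plan, and the absence of a missing-data rule is not the point made here. It does not remove the problem: the article itself fixes the question as one about response after the wait, fixes Cohort 2's starting value at the end of the wait, and names tests that need both readings.

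A reader might go further and infer that the check is biased towards finding no impact, on the view that families who persist are the more motivated. The documents do not support that. They say nothing about who leaves, and even if the more responsive families stay, the contrast moves towards zero only when waiting truly reduces response.

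The size is also open to challenge. The second 30% loss and every correlation are assumptions. The upper end needs 30% loss and r = 0.5 together, and a looser link between response and leaving gives less. The planned 0.6 belongs to another contrast, so it is not a benchmark here.

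Finally, the waitlist question is exploratory and opens only a supplementary estimate. That limits the consequences and is accepted.

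**Conclusion.** The point holds in a limited form. As worded, the waitlist contrast conditions Cohort 2 on a post-randomisation event that Cohort 1 never faces, and its result decides pooling. Differential loss during the wait can therefore hide, create or distort a waitlist effect. The direction is unknown. The size is about 0.04-0.25 SD under assumed loss of 10-30% and assumed correlations of 0.2-0.5, and nil if leaving is unrelated to response. The primary comparison from baseline to 10 weeks is not affected, because it does not depend on Cohort 2 going on to receive the program. The change is worth making because it is cheap and the pooled estimate inherits the same selection.

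**What to change.** In Section 2.7, or in the analysis plan if one exists:

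- Analyse the waitlist contrast with a likelihood-based mixed model that includes every randomised child and uses the baseline and post-wait readings, so that families lost during the wait still contribute what they provided.
- Report the proportions starting and completing the program among all randomised families, by cohort, as risk differences with 95% confidence intervals. Weigh these alongside the outcome comparison before deciding to pool.
- Label any starters-only comparison, and any pooled pre-post comparison, as non-randomised.

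The cost is a little more analysis. Section 2.5 says that information collected during program administration is held in the provider's system. Start and completion are probably recorded there, but the article does not say so and this should be confirmed. The model rests on a missing-at-random assumption, which should be stated. The waitlist or pooled result may also turn out less favourable.

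### The pooled one-way repeated measures ANOVA has no control group, so it cannot give the program's effect size with greater certainty, and finding no waitlist impact does not justify the pooling

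*Protocol article*

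**What the plan says.** Section 2.7 (Data Analysis) first sets out the randomised comparisons: an independent t-test of Cohort 1 against Cohort 2 on change in BMI z-score to 10 weeks, and mixed ANOVAs that keep the control group. It then says that the effect of having waited will be explored by comparing Cohort 2 with Cohort 1 over time. The condition for the next step reads: "If being waitlisted does not have an impact on the quantitative outcome measures (as anticipated), a one-way repeated measures ANOVA will be used". The purpose that the article gives for this ANOVA is "to assess the effect size of the web-based program on quantitative outcome measures overtime with greater certainty (i.e., power").

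The article does not use the word pooling. It follows from the method, because a one-way repeated measures ANOVA has time as its only factor. It also fits the next sentence of Section 2.7, which describes a before-and-after comparison in all participants. The starting point there is baseline for Cohort 1 and the end of the wait for Cohort 2.

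Section 2.2 says that control families "will receive the (same) web-based program in the school term or midterm following the waitlist control term". Section 2.3.2 gives the only power calculation, for the randomised contrast. It also says that the calculation allowed for some fall in BMI z-score among controls.

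**The concern.** Two things are wrong with this step.

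First, the quantity is mislabelled. Change within children from before to after the program contains whatever would have happened anyway: background trend, season, the effect of repeated self-measurement, and regression to the mean after selection on a BMI at or above the 85th percentile. Only the untreated arm can remove these, and this analysis drops it. A larger sample narrows the interval around a biased quantity.

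Second, the condition treats failure to find a waitlist effect as grounds for pooling. No margin says how small a difference must be to count as no impact, and the trial was sized for a much larger difference.

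The stake is interpretation. The aims in Section 1 cover outcomes immediately after the program and at 6 and 12 months. By the later visits Cohort 2 has had or started the program, so no untreated group remains. Uncontrolled change is all the design offers there, and Section 2.7 describes it as an effect size known with more certainty. That invites a reader to rank it above the randomised estimate.

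**Working it through.** **Inputs from the plan**
- Significance and power: "With a 5% significance and 80% power" (Section 2.3.2). Sidedness is not stated; two-sided is assumed because only that reproduces the sample size.
- Effect size: "The effect size based on the change in BMI z-score and informed by pilot data was 0.6" (Section 2.3.2).
- Allocation: "The randomization schedule was generated using block randomization (1:1 ratio") (Section 2.2).
- Attrition: "a 30% attrition rate based on previous trials on a similar program" (Section 2.3.2).
- Target: "this study aims to recruit *n* = 118 participants", 59 per group (Section 2.3.2).

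**Step 1. Reproduce the plan's figure.** A two-sample t-test with d = 0.6, two-sided 5% and 80% power needs 44.6, so 45 per group (noncentral t). Then 45 × 1.3 = 58.5, so 59 per group and 118 in total, which matches. After 30% loss, 59 × 0.7 = 41.3, so about 41 per cohort and 82 pooled. The ranges below run from 41 per cohort (30% loss) to 59 (no loss).

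**Step 2. Power of the waitlist check.** Section 2.7 names no test. Assume a two-sided 5% t-test between cohorts on pre-to-post-program change, with a true difference of d SD. The noncentrality is d × √(n/2). For d = 0.3 this is 0.3 × √20.5 = 1.36 with 41 per cohort and 0.3 × √29.5 = 1.63 with 59.

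| True cohort difference | 41 per cohort | 59 per cohort |
|---|---|---|
| 0.2 SD | 15% | 19% |
| 0.3 SD | 27% | 37% |
| 0.4 SD | 43% | 58% |
| Difference with 80% power | 0.63 SD | 0.52 SD |

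A true 0.3 SD difference would be missed in 73% (100 − 27) or 63% (100 − 37) of trials. The 95% CI half-width for the cohort difference is t × √(2/n): 1.99 × √(2/41) = 0.44 SD, or 1.98 × √(2/59) = 0.36 to 0.37 SD. Even an observed difference of zero would leave 0.3 SD inside the interval.

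For scale, take a formal equivalence test (two one-sided 5% tests, 80% power, true difference zero) with an assumed margin of 0.3 SD. It needs 2 × ((1.645 + 1.282)/0.3)², about 191 per cohort. For a margin of 0.2 SD it needs 429.

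**Step 3. What the pooled analysis would credit to the program.** Suppose the program does nothing and there is a background change of δ SD of the change scores. The plan gives no size for this, so δ is assumed. With two time points, a one-way repeated measures ANOVA equals a paired t-test with noncentrality δ × √N. For δ = 0.2 this is 0.2 × √82 = 1.81 and 0.2 × √118 = 2.17.

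| Assumed background change | 82 pooled | 118 pooled |
|---|---|---|
| 0.2 SD | 43% significant | 58% significant |
| 0.3 SD | 77% significant | 90% significant |

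The false-positive rate rises with the sample size, which is the opposite of greater certainty about the program.

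**Step 4. Timing.** Within one recruitment cycle, Cohort 2 takes the program in a later term or midterm than Cohort 1. A simple cohort comparison therefore mixes any waitlist effect with a term effect.

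**The case against.** The strongest defence is that this is a conditional, secondary analysis. The randomised t-test and the mixed ANOVA with a control group come first and answer the primary question, and the secondary outcomes have randomised 10-week comparisons too. That is correct and limits the reach of the point.

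Several stronger readings are tempting and are not supported:

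- **Pooling will nearly always go ahead, valid or not.** A reader might infer this from the low power. It applies only to modest differences: with 41 per cohort, power is 61% at 0.5 SD and 77% at 0.6 SD. The condition also refers to outcome measures in the plural, and Section 2.7 lists at least five. If every one had to show no impact, with 0.3 SD on each and independent outcomes, pooling would proceed in about 0.731⁵ = 21% of trials. The text does not settle which reading applies.
- **The plan treats a non-significant result as proof of no effect.** No test or threshold is named, so this is inference. What the text does show is a condition with no equivalence margin.
- **Waitlist and season can never be separated.** Section 2.2 describes repeated recruitment cycles, so Cohort 2 of one cycle can share a term with Cohort 1 of a later one. The confounding is complete only within a cycle, and term can be adjusted for across cycles.
- **Numbers fall further after a second 30% loss.** The plan gives one attrition figure, and only Cohort 2 has a second period before its post-program visit.
- **Growth biases the main result.** BMI z-score is standardised for age and sex, so ordinary growth is largely removed. Regression to the mean is also weaker in Cohort 2, whose starting value is taken after the wait.

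None of this supplies the missing control group. Background trend, season and repeated self-measurement remain, and Section 2.3.2 itself allows for change without the program.

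**Conclusion.** The point holds for the secondary analysis. The pooled one-way repeated measures ANOVA estimates uncontrolled within-child change. Describing it as the program's effect size with more certainty is wrong as written, and that conclusion needs no assumed figure. The condition does not rescue it: even if waiting truly had no impact, the pooled change would still lack a control.

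The sizes are illustrations. The false-positive rates of 43% to 58% rest on an assumed background change of 0.2 SD and two time points. The power of 27% to 37% rests on an assumed two-sided 5% t-test and a 0.3 SD cohort difference.

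A reader might infer that the trial's main result is compromised. It is not: the primary randomised comparison and the sample size do not depend on this step.

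**What to change.** In Section 2.7:

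- Remove the condition, so that nothing depends on finding no waitlist impact.
- Always report the between-cohort difference in pre-to-post-program change with its 95% CI, alongside the changes by cohort and averaged over cohorts. A mixed model with program phase, cohort and their interaction is one suitable way but not the only one. Adjust for term across recruitment cycles, or say that the cohort difference includes any term effect.
- Label these results as uncontrolled within-child change.
- Delete the stated purpose, "to assess the effect size of the web-based program on quantitative outcome measures overtime with greater certainty (i.e., power").
- State that the randomised baseline-to-10-week contrast is the only estimate of the program's effect.

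This changes the analysis wording and uses the same data. The cost is that the claim of extra power for the program effect is lost.
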